
### Aim and Scope

The purpose of this paper is to present the research protocol and recruitment process that will be employed for a randomized controlled trial (RCT) to evaluate the efficacy of NoiBene as a group intervention (NB-G). This condition will be compared with two other conditions: NoiBene as a guided web-based intervention (NB-WB) and with a waiting list condition (WLC). We hypothesized that participants in the NoiBene conditions (both NB-G and NB-WB), compared with participants in the WLC, would show after the intervention higher levels of mental health and well-being (Cuijpers et al., 2021) as well as an increase in academic performance and satisfaction (Bean and Eaton, 2001). We also predict that students in the NoiBene conditions will increase their emotional awareness and assertiveness, and they will reduce the level of perfectionism, repetitive thinking, and experiential avoidance (Di Consiglio et al., 2021a). However, we hypothesized that the NB-G conditions will be more effective than the NB-WB in improving assertiveness, since the group context guarantees more supervised practice (Salas and Cannon-Bowers, 2001; Gresham, 2002; Taylor et al., 2005), and it ensures a positive environment where the member can interact in an adaptive manner (Yalom, 1985). However, besides treatment efficacy, we expect that students can benefit from the NB-G or NB-WB differently based on their specific behavioral and motivational patterns. For example, bases on specific personality traits or set of values students could be more motivated to participate and benefit more from a guided web-based intervention or from a group intervention.

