## Methods

### Participants

Seventy-five (*n* = 75) students will be voluntarily recruited from different universities in Rome, Italy. The sample size for this study was determined based on power analysis using G*Power 3.1.9.7 (Faul et al., 2007). We calculated that the minimum required sample size to detect an effect size of *f* = 0.25 using a mixed analysis of variance (ANOVA) including within-subject (3-time points) and between-subject (3 groups) effects with 95% power and at a two-sided 5% significance level was 54 participants (18 per treatment arm). However, attrition is a common problem that occurs in RCT: around 20% of participants withdraw before completing the study protocol (Mason, 1999). In conclusion, we plan to recruit approximately 75 participants (25 per treatment arm).

NoiBene will be advertised by word of mouth, mailing lists, and sharing fliers on various social networks (i.e., Facebook, Instagram). Students will be informed about the implementation of a group intervention to promote well-being and to prevent psychological distress. They will receive information about the program and about the specific goal of the intervention. The organization and the calendar of the meetings will also be presented. Since many university courses include credits achievable by practical activities (highly specialized workshops), all participants will receive an intervention completion certificate that they can use to achieve such credits.

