## Statistical Analysis

Data will be processed using SPSS (IBM) version 27. Descriptive analysis will be run for all the sociodemographic and academic variables, on data related to the satisfaction questionnaires and on SCL-90-R and MCMI-III scores. Chi-Square tests will be used to investigate differences between participants in the three conditions on baseline demographic variables and gender variables. With the same aim, a series of Student’s *t*-test will be run on age variable and on all baseline measures. If the test will provide significant *p*-values, effect sizes will be calculated considering Cohen’s d (small > 0.20, medium > 0.50, large > 0.80). If some variables will result significantly different between conditions, they will be included as covariant in the further analysis. A series of mixed models of analysis of variance (ANOVAs) will be run to investigate the efficacy of the intervention on the PWBI, WEMWBS, TAS-20, SIB, MPS, LOSC, RRS, PSWQ, and AAQ scores, as a function of the factor between CONDITION (NB-G vs. NB-WB vs. WLC) and the factor within TIME (Baseline vs. Post-Intervention vs. Follow-Up). The level of significance was set at *p* < 0.05. Effect sizes will be calculated using partial eta squared and it will be interpreted based on benchmarks suggested by Cohen (2013): *n*^2^ = 0.01, small effect size; *n*^2^ = 0.06, medium effect size; *n*^2^ = 0.14 large effect size. The *post hoc* analyses of significant interaction will be conducted using the Bonferroni *post hoc* test.

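### Bonferroni across the three arm pairs is valid but needlessly conservative; Holm's step-down test over the same pairs keeps the 5% error rate and never rejects less

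*Protocol article*

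**What the plan says.** The Statistical Analysis section runs a mixed ANOVA on each outcome, with "the factor between CONDITION (NB-G vs. NB-WB vs. WLC") and "the factor within TIME (Baseline vs. Post-Intervention vs. Follow-Up"). It adds: "The level of significance was set at *p* < 0.05". Post hoc "analyses of significant interaction will be conducted using the Bonferroni" test. No contrasts are named, the family is not restricted, and no adjusted threshold is printed.

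Aim and Scope gives the hypotheses that the pairwise tests must serve. For well-being, it predicts that "participants in the NoiBene conditions (both NB-G and NB-WB), compared with participants in the WLC, would show after the intervention higher levels". Between the two formats it predicts a difference on one outcome only: "we hypothesized that the NB-G conditions will be more effective than the NB-WB in improving assertiveness". The same section also names NB-WB, next to the waiting list, as a condition with which NB-G is to be compared.

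**The concern.** The omnibus interaction test does not say which arm differs from which. Every statement about a particular arm therefore comes from the post hoc step, and the adjustment used there decides how often a true benefit is reported.

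Bonferroni holds all three pairs at 0.0167, even after one or two differences have been established. A step-down procedure relaxes the threshold for the remaining pairs and keeps the same error guarantee. The main claim is that both formats beat the waiting list, with about 20 completers per arm. The second comparison can therefore miss a threshold that it did not need to meet, and a real benefit of one format would be reported as not shown. The same applies to NB-G against NB-WB on assertiveness, the only predicted difference between formats.

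**Working it through.** **Inputs from the protocol article.** There are three arms and three time points (Statistical Analysis). The target is to "detect an effect size of *f* = 0.25", "with 95% power and at a two-sided 5% significance level was 54 participants (18 per treatment arm"). Recruitment is 75 students, 25 per arm, with about 20% attrition (Participants). Completers: 25 × 0.8 = 20 per arm.

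**Assumed, because not stated.** Correlation between time points 0.5, sphericity, unit SD, a gain present at post-intervention and kept at follow-up, and a family of three arm pairs.

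**The plan's own figure.** For the group-by-time interaction, the noncentrality is λ = f²·N·m/(1−ρ), with (k−1)(m−1) and (N−k)(m−1) degrees of freedom. With N = 54, k = m = 3 and ρ = 0.5, λ = 0.0625 × 54 × 3 / 0.5 = 20.25 on 4 and 102 df. Power is 0.958, so the stated 54 is reproduced. It is the power of the omnibus interaction; the pairwise tests are not covered by it.

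**What f = 0.25 means for one arm pair.** Let both NoiBene arms gain d SD at post-intervention and follow-up, and the waiting list gain nothing. The squared interaction effects of the nine cell means sum to 4d²/9, so λ = (N/3)(4d²/9)/(1−ρ). Setting this equal to f²·N·3/(1−ρ) gives d² = (81/4)f², so d = 4.5 × 0.25 = 1.125 SD.

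**Thresholds.** Bonferroni: 0.05/3 = 0.0167 for every pair. Holm: smallest p against 0.05/3 = 0.0167, next against 0.05/2 = 0.025, last against 0.05, stopping at the first failure.

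**Why Holm costs no error control.** Each Holm threshold is at least 0.0167, so whatever Bonferroni rejects, Holm rejects. Suppose m₀ of the three null hypotheses are true. The first true one that could be rejected meets a threshold of at most 0.05/m₀, so the chance of any false rejection is at most m₀ × 0.05/m₀ = 0.05. This needs no assumption on effects, correlation or attrition.

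**Size of the gain.** Simulated trials: 20 per arm, interaction F test required at 0.05, then pooled-variance t tests at post-intervention.

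| What is to be shown | True effect (SD) | Bonferroni | Holm, three pairs |
|---|---|---|---|
| Both NoiBene arms better than WLC | 0.6, 0.6 | 10% | 12% |
| Both NoiBene arms better than WLC | 0.8, 0.8 | 31% | 36% |
| Both NoiBene arms better than WLC | 1.0, 1.0 | 60% | 66% |
| Both NoiBene arms better than WLC | 1.125, 1.125 | 76% | 81% |
| NB-G better than NB-WB (assertiveness) | 1.2, 0.6 | 28% | 36–37% |

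Repeated runs agreed within about one percentage point. Testing change from baseline instead gives 36% and 42% for both arms at 0.8 SD.

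**What does not improve.** Holm's first step is Bonferroni's threshold, so the chance of rejecting at least one of the three pairs is identical. With equal benefits of 0.8 SD, the chance of showing at least one NoiBene arm better than the waiting list is about 55% under either method. Per-comparison power at 1.125 SD moves only from 84% to 86%.

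**Error check.** With no effect anywhere and no interaction test required first, the simulated family-wise error was 4.1% to 4.5%, the same for both methods.

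**The case against.** Bonferroni is pre-specified, controls the error, and yields adjusted p-values and matching intervals together. The section states nothing false and contradicts nothing, so the choice can be called a matter of preference. It is true that no validity problem exists. But Holm over the same pairs dominates Bonferroni as a test, so the only real trade is against the matching intervals.

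The gain from Holm alone is modest. Among trials at 0.8 SD in which Bonferroni shows exactly one NoiBene arm better (55.0% − 30.5% = 24.5%), Holm rescues the second in 5.0/24.5, or about 20%. Small arms explain most of the remaining failures. This stands.

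The three-pair family is inferred. This also stands, and the 0.0167 should be read as the natural interpretation of an unrestricted post hoc test on a three-level factor.

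A reader might go further and infer that, on PGWBI and WEMWBS, a third of the error rate is wasted on a comparison nobody planned, and that Holm returns all the power lost. The document does not support this. It predicts no well-being difference between the formats, but Aim and Scope does list NB-WB as a comparator for NB-G, so keeping that pair in the family is defensible. Limiting the well-being family to the two waiting-list comparisons would raise the chance of showing both to about 44–45% at 0.8 SD. The step beyond 36% comes from dropping a comparison, which is a separate decision from the choice of procedure.

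**Conclusion.** The point holds as an avoidable loss of efficiency. At the same 5% family-wise error, Holm over the three pairs adds about 5 to 6 percentage points to the chance of showing both NoiBene arms better than the waiting list for true benefits of 0.8 to 1.125 SD. It adds about 8 to 9 points for NB-G over NB-WB on assertiveness at 1.2 against 0.6 SD. The direction is certain for any fixed family. The size depends on the assumed 20 completers per arm, correlation of 0.5, equal gains kept at follow-up (for the comparisons with the waiting list) and three-pair family.

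The 5% here refers to one outcome at one time contrast. Two primary scales and two post-baseline times raise a separate multiplicity question that this change does not address.

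**What to change.** In the Statistical Analysis section, replace the Bonferroni post hoc test by Holm-adjusted pairwise comparisons over the three arm pairs, applied to the unadjusted p-values, and write the three pairs out. The cost is one sentence and a short hand calculation on the SPSS output. Because Holm has no simple matching simultaneous intervals, report unadjusted 95% intervals (or Bonferroni intervals) alongside and label them as such.

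Optionally, the sponsor may limit the PGWBI and WEMWBS family to NB-G against WLC and NB-WB against WLC (smaller p against 0.025, the other against 0.05) and give NB-G against NB-WB as an estimate with its interval. This fits the directional well-being hypothesis but gives up a confirmatory test of a comparison that Aim and Scope lists, so it must be decided before any data are seen. For assertiveness all three pairs stay in the family.

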## Expected Results and Discussion

Mostly, mental health disorders have the first onset by 24 years (Kessler et al., 2007; De Girolamo et al., 2019). University years, which coincide with this critical period, represent a crucial moment in every student’s life. Recent evidence suggested that mental health problems are prevalent among university students (Auerbach et al., 2018). Such problems may affect students’ lives and lead to a personal, relationship, and academic difficulties (Alonso et al., 2018; Bruffaerts et al., 2018). Over the past decades, the awareness about the importance of implementing strategies for promotion and prevention has exponentially grown. In this field, we developed the NoiBene intervention, a program to improve students mental health and well-being, and to prevent mental health disorders.

We expect that participants in the NoiBene conditions will show a higher level of mental and psychological well-being after the intervention than the waiting list condition. Indeed, NoiBene includes a series of interventions to increase some fundamental life skills, such as emotional awareness, assertiveness, and goal setting, elements that have an important role in determining mental health (Savoji and Ganji, 2013). Moreover, it provides a series of interventions focusing on self-acceptance-related emotions, an important factor that positively affects mental health (Rash et al., 2011; Weiss et al., 2016). Lastly, the NoiBene conditions include a psychoeducation about healthy lifestyles; students are then encouraged to link them with their own values and to set goals according to them. A broad range of evidence suggests that healthy lifestyle interventions are associated with mental health and well-being improvements (Dale et al., 2014). We also predicted that participants in the NoiBene condition will improve their academic performance and satisfaction. Indeed, the NoiBene program includes contents about the study method, and it could contribute to improving their performance and study skills (Meneghetti et al., 2016). Moreover, the psychological well-being of university students is an important factor in successfully dealing with the demands of academic life. High levels of well-being promote the adoption of more adaptive coping strategies, such as positive reappraisal of the problems and help-seeking behaviors (Freire et al., 2016). Furthermore, higher levels of well-being positively impact personal growth and academic achievements (Bowman, 2010; Bordbar et al., 2011; Yu et al., 2018). We hypothesized that participants in the NoiBene conditions will decrease levels of repetitive thinking, perfectionism, and experiential avoidance (Di Consiglio et al., 2021a). We expect that the reduction of these dysfunctional process can reduce the level of specific symptoms such as anxiety and depression and can buffer against the development of future mental disorders (Frank and Davidson, 2014).

Moreover, we believe that the group protocol could be even more effective than the guided web-based protocol in improving assertiveness (Conley et al., 2013), since the group protocol ensures supervised skills practice over multiple sessions, an essential component of successful training (Salas and Cannon-Bowers, 2001; Gresham, 2002; Taylor et al., 2005). Moreover, some unique characteristics of the group can foster this positive change. For example, the group ensure a positive environment where the member can interact in an adaptive manner and can engage in positive relationship; also, the group context ensure the modeling process both from the Tutor and from other member and imitative behaviors are an important source of learning (Yalom, 1985; Johnson et al., 2005) unlike the individual guided intervention. However, we believe that it is important to consider that students can benefit from the NB-G or NB-WB differently based on their specific behavioral and motivational patterns. For example, values are an important broad motivator of actions and affect prosocial behavior (Schwartz, 1992). Values such as benevolence and conformity promote cooperative and supportive social relations. Indeed, these values motivate actions to promote the welfare of others and to avoid adverse outcomes for self. Conversely, values such as security and power usually oppose prosocial behavior since they motivate to maintain a stable and protective environment and emphasize self-interest (Schwartz, 2010). Students guided by such values could be more motivated to participate and benefit more from a group intervention or from a guided self-help intervention, respectively. This consideration is significant if we also consider the clinical utility of these interventions. This dimension concerns the extent to which the intervention will be effective in a real-world practical setting (American Psychological Association, 1995). Moreover, when proposing an intervention, it is important to consider not only the best available intervention but also the individual characteristics and preferences (American Psychological Association Presidential Task Force on Evidence-Based Practice, 2006). Therefore, outside a controlled empirical context, we expect that students will report a preference toward a group or guided self-help intervention based on personal characteristics.

Students in the NoiBene conditions will receive a series of theoretical information about well-being and factors that contribute to mental health or mental disorders. We expect that this increasing knowledge would foster a better attitude toward help-seeking behavior (Jorm et al., 1997; Gulliver et al., 2010). Moreover, we will conduct psychodiagnostics interviews and feedback meetings with students reporting high levels of psychological distress. In the case of psychopathology, we will have the opportunity to give personalized feedback about students’ symptomatology, discuss their personal barriers that hinder the help-seeking behavior, and inform them about how and where to find help in the area. It could be an efficacious strategy to encourage the request for help (Gulliver et al., 2010; Di Consiglio et al., 2021b).

In conclusion, NoiBene presents a series of strengths and practical implications. Although interventions targeting specific areas of functioning are important, NoiBene has the advantage that it is a comprehensive program built on a eudemonic (Ryff and Keyes, 1995) and hedonic (Kahneman et al., 1999) approach to well-being. Indeed, NoiBene aims to promote self-realization and foster positive affect. Moreover, NoiBene focuses on a series of essential transversal competence (e.g., emotional awareness, assertiveness, goal setting), covering a range of variables necessary for mental health. Second, most of the preventing trials are focused on specific issues such as depression, anxiety, and stress (see Cuijpers et al., 2021 for a review). NoiBene has been developed on a transdiagnostic approach: it considers three of the main factors occurring in many mental health disorders such as repetitive thinking, perfectionism, and experiential avoidance (Frank and Davidson, 2014). It means that the activities that NoiBene proposes do not focus on specific symptoms or disorders but instead focus on dysfunctional processes that may contribute to the development of psychopathology. For this reason, we expect that it can be helpful the reduce the risk of the development of different mental disorders. Lastly, it is important to consider that besides negative consequences on individual students’ quality of life, the high prevalence of mental disorders and psychological distress among students is also critical for universities. Indeed, it can hurt academic performance and participation (Eisenberg et al., 2007; Reavley and Jorm, 2010; Buchanan, 2012), and protracted psychological distress leads to reduced self-efficacy, motivation, and academic satisfaction (Lipson and Eisenberg, 2018). Moreover, emotional problems seem to be the most common reason students drop out during the first year of university (Baik et al., 2015). Therefore, NoiBene could provide the opportunity to integrate health into university culture and foster a positive environment that can implicate benefits for students and the entire university community.
